# Scaling Up Safer Birth Bundle Through Quality Improvement in Nepal (SUSTAIN)—a stepped wedge cluster randomized controlled trial in public hospitals

**DOI:** 10.1186/s13012-019-0917-z

**Published:** 2019-06-19

**Keywords:** Quality improvement interventions, Basic neonatal resuscitation, Fetal heart rate monitoring, Stepped wedge cluster randomized control trial, Nepal

## Abstract

**Background:**

Each year, 2.2 million intrapartum-related deaths (intrapartum stillbirths and first day neonatal deaths) occur worldwide with 99% of them taking place in low- and middle-income countries. Despite the accelerated increase in the proportion of deliveries taking place in health facilities in these settings, the stillborn and neonatal mortality rates have not reduced proportionately. Poor quality of care in health facilities is attributed to two-thirds of these deaths. Improving quality of care during the intrapartum period needs investments in evidence-based interventions. We aim to evaluate the quality improvement package—Scaling Up Safer Bundle Through Quality Improvement in Nepal (SUSTAIN)—on intrapartum care and intrapartum-related mortality in public hospitals of Nepal.

**Methods:**

We will conduct a stepped wedge cluster randomized controlled trial in eight public hospitals with each having least 3000 deliveries a year. Each hospital will represent a cluster with an intervention transition period of 2 months in each. With a level of significance of 95%, the statistical power of 90% and an intra-cluster correlation of 0.00015, a study period of 19 months should detect at least a 15% change in intrapartum-related mortality. Quality improvement training, mentoring, systematic feedback, and a continuous improvement cycle will be instituted based on bottleneck analyses in each hospital. All concerned health workers will be trained on standard basic neonatal resuscitation and essential newborn care. Portable fetal heart monitors (Moyo®) and neonatal heart rate monitors (Neobeat®) will be introduced in the hospitals to identify fetal distress during labor and to improve neonatal resuscitation. Independent research teams will collect data in each hospital on intervention inputs, processes, and outcomes by reviewing records and carrying out observations and interviews. The dose-response effect will be evaluated through process evaluations.

**Discussion:**

With the global momentum to improve quality of intrapartum care, better understanding of QI package within a health facility context is important. The proposed package is based on experiences from a similar previous scale-up trial carried out in Nepal. The proposed evaluation will provide evidence on QI package and technology for implementation and scale up in similar settings.

**Trial registration number:**

ISRCTN16741720. Registered on 2 March 2019.

## Background

The accelerated reduction in maternal and child mortality during the Millennium Development Goal era (2000–2015) led to the realization that further reduction can only be achieved with improved quality of care in the intrapartum period [1, 2]. Every year, almost 1.2 million stillbirths and 250,000 maternal deaths occur during the intrapartum period, and a million newborns die in their first day of life [3–5]. The United Nations’ Every Woman and Every Child strategy 2016–2030 aims to reduce preventable maternal, neonatal, and child deaths by the end of the Sustainable Development period 2030 [6]. The strategy has resulted in a number of efforts to identify ways of reducing preventable deaths [7]. One of the key initiatives was led by the Lancet Global Health Commission for High Quality Health Systems in the SDG Era [8]. Through consultations and systematic reviews, the commission produced a framework for improved quality of care in health care settings [9, 10]. Its five foundations are (1) understanding populations’ health care needs; (2) strengthening structures and governance for improving quality of care at all levels of health systems [11]; (3) redesigning and optimizing the health workforce to provide a more conducive environment for health care provision; (4) introducing new tools, quality improvement interventions, and technologies for delivering health care; and (5) the adequacy or capacity of health facilities to deliver health care as per the demands of their client populations [8].

The PARiHS framework (Promoting Action on Research Implementation in Health Services) promotes the translation of evidence into practice using context and facilitation as interplay for improving quality of care [12, 13]. This is a useful framework as two-thirds of premature and preventable neonatal death are due to poor quality health care and *not to* lack of access to health care [14]. The large investments made in improving access to and the availability of maternal and newborn care since the start of the MDG period in 2001 [15] had a large impact on reducing the extent of the first and second delays of maternal and newborn care [16]. However, the third delay of inadequate quality of care remains a large challenge [17, 18].

In Nepal, several studies have found inadequate quality of care as a major barrier to reducing maternal and neonatal deaths, especially during the intrapartum period [19, 20]. The following approaches for quality improvement have been effective in low-income settings to overcome this barrier [21–23]:Understanding the context in which health facilities operate, and based on this improving leadership to bring about organizational improvements [24];Facilitating quality improvement through external and internal drivers such as mentoring and feedback from audits [25] for bringing improvements in clinical units [26].Introducing new standards and tools for improving efficiency to implement the standards.Setting up data platforms for instigating accountability for the provision of quality care [27].

The actual ‘dose-response’ of the above four approaches will depend upon the adequacy of QI package implementation and the context of implementation [28].

The implementation research will examine the impact of a new quality improvement project—–the Scaling Up Birth Bundle Through Quality Improvement in Nepal (SUSTAIN). The SUSTAIN project aims to improve intrapartum care through a set of quality improvement interventions (Fig. 1). The interventions are based on learning from our previous implementation research on quality improvement for intrapartum care [29].

**Fig. 1 Fig1:**
[figure not shown]
Intervention design of the SUSTAIN package

The objective of the research is to evaluate:The impact of the SUSTAIN package on intrapartum-related mortality;The impact of the package on health workers’ performance on monitoring fetal heart rates, essential newborn care, and neonatal resuscitation;The appropriateness of implementing the quality improvement interventions in the hospitals [30]; andThe acceptability of the SUSTAIN package in the hospitals.The perception of women for intrapartum care

## Methods

### Trial design

The trial is a stepped wedge cluster randomized controlled trial in eight public hospitals in Nepal. Each hospital will represent a cluster randomized in a cross-sectional wedge design with intervention transition period in each hospital in 2 months (Fig. 2). With the qualitative research components, we aim to provide insight into women’s and staffs’ response to intervention and to understand how contextual factor affect its implementation [31].

**Fig. 2 Fig2:**
[figure not shown]
Stepped wedge cluster randomized controlled design. Note: gray shading is the control period, white is the implementation transition period, and dark blue is the intervention period

### Settings

Each hospital manages at least 3000 deliveries a year (Table 1). Their intrapartum-related mortality rates range from 11 to 36.5 intrapartum-related deaths (intrapartum stillbirth and first-day mortality) per 1000 births. All the hospitals have separate labor units and operating theaters. Normal and complicated vaginal deliveries take place in the labor units and cesarean sections in the operating theaters. Each hospital has a postnatal unit and a sick newborn care unit. The hospitals provide level II sick newborn care services [32].

**Table 1 Tab1:** Total birth and mortality rate in the study hospitals (2017)

	Total no. births	Intrapartum stillbirth rate (per 1000 births)	First-day neonatal mortality rate (per 1000 live births)	Intrapartum-related death rate (per 1000 births)
Koshi Zonal Hospital	5464	9.3	4.4	13.7
Janakpur Regional Hospital	14,300	11.9	23	34.9
Bharatpur Hospital	11,006	7.3	3.7	11.0
Lumbini Zonal Hospital	8649	11.2	12.3	23.5
Dadeldhura Sub-Regional Hospital	3112	10.3	4.4	14.7
Mid-Western Regional Hospital	3847	5.0	25	30.0
Bheri Zonal Hospital	4132	1.2	35.3	36.5
Seti Zonal Hospital	6277	2.2	29.7	27.9

Intrapartu-related mortality is the composite of intrapartum stillbirths and first-day mortality data

#### Participants

##### Eligible criteria for participants

The study will cover pregnant women with a gestational age of more than 22 weeks admitted to hospital with fetal heart sound at admission who consent to be enrolled in the study. The process evaluation data are collected from staff members working in the labor and delivery room in the study sites.

#### Interventions

The SUSTAIN package is a bundled QI package to empower health care workers to provide improved care and to review its provision during the intrapartum and immediate postpartum periods. The interventions include training and technology for intrapartum monitoring, neonatal resuscitation, and a supporting system to review the implementation of these measures.

The SUSTAIN interventions in the hospitals will be as follows:The bottleneck analysis of delivery care and setting up mechanisms to review and plan improved care and improve accountability.The introduction of the Safer Births Bundle, which is a set of tools for training and therapy to improve the monitoring of labor (using Moyo FHR monitors®) [33] and neonatal resuscitation (using upright bag-masks® [34], NeoBeat® newborn heart rate meters and NeoNatalie live training manikins®).The implementation of QI interventions in delivery rooms including daily skill checks on neonatal resuscitation, using checklists to prepare for births and resuscitation, using self-review evaluation checklists after neonatal resuscitation incidents, and holding weekly review meetings to track progress on implementing the new tools and standards.The setting up of a system to continuously measure the quality of intrapartum care using the Plan-Do-Study-Act (PDSA) approach [35]. This approach harnesses the local ownership of challenges and provides an actionable framework to monitor and evaluate progress to improve and sustain QI changes.

In the project using the i-PARISH framework, facilitation is done at three different levels of types of facilitators. First, an external facilitator or mentor who introduces the innovation of SUSTAIN to the hospital leadership and conducts an assessment of the hospital context in terms of implementing the innovation. The external facilitator will be an expert to coordinate with the different networks of facilitators. The external facilitators conduct bottleneck analysis workshop, plan meeting, and supervise the internal facilitators. Second, an experienced internal facilitator has a deeper understanding of the organization local context. The facilitator conducts training on the intervention package and the rolls out of the innovations (safer births bundle). Third, an internal new facilitator will be working under the supervision of the experienced internal facilitator to implement the daily skill checks on neonatal resuscitation, using checklists to prepare for births and resuscitation, using self-review evaluation checklists after neonatal resuscitation incidents, and conducting PDSA meeting.

### Outcomes

Primary outcome*Intrapartum-related mortality*—intrapartum-related mortality defined as intrapartum stillbirth (no breathing 10 min after delivery) and neonatal death within the first 24 h of life [36].

Secondary outcomes:Proportion of deliveries with fetal heart rate monitoring as per standard protocol.Proportion of deliveries in which abnormal fetal heart rate during labor is followed by neonatal resuscitation.Proportion of deliveries resulting in emergency cesarean sections and instrumental deliveries due to fetal distress.Proportion of non-breathing babies who receive a bag and mask ventilation within 1 min of birth.Proportion of health workers maintaining neonatal resuscitation skills 6 months after being trained on it.Adequacy and acceptability of the implementation of SUSTAIN package

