### Data collection

An independent team will be established in each hospital to collect data on implementation, process, and outcomes.

*Implementation level data—*a form will be used to collect data on the number of stakeholders engaged in each intervention:A hospital readiness and service availability assessment tool will be used to conduct the bottleneck analysis of service readiness for intrapartum care. A planning tool will be used to develop a plan based on the bottleneck analysis.Data on health workers’ knowledge and skills on intrapartum care before and after training will be collected using multiple-choice questions and skills checklist.The data on the continuous quality improvement process will be collected using a Plan-Do-Study-Act diary, which was tested in our previous study [21].The periodic performance of the health workers will be done using a skills checklist.

*Process level data—*A separate system will be established to collect data on health worker performance in simulated and clinical intrapartum care settings:Data will be collected on the use of the NeoNatalie Live® manikin through skill drills in an application-based system.The use of fetal heart rate monitor (Neobeat®) will be assessed by a separate group of data collector using an observation checklistData on health worker performance on monitoring fetal heart rates, immediate newborn care, and neonatal resuscitation will be collected using an observation checklist.The implementation of the SUSTAIN interventions using the PARIHS framework [39] will be evaluated through in-depth interviews and focus group discussions with service providers and caregivers.The acceptability of the new interventions will be assessed by studying health worker acceptance and barriers to use.The perceptions of women about intrapartum care will be evaluated with semi-structured interviews.

*Outcome level data—*data on mortality and clinical events during intrapartum care will be collected from patient case notes and labor and delivery registers.

*Socio-demographic data—*the socio-demographic characteristics of the women will be collected through semi-structured interviews.

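### The stillbirth component of the primary mortality outcome rests on absence of breathing at 10 minutes, so as written an infant who survives beyond 24 h can count as a death

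*Protocol article*

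**What the plan says.** In the protocol article, Outcomes, the primary outcome is intrapartum-related mortality, a composite of two components. The first is "intrapartum stillbirth (no breathing 10 min after delivery", with the parenthesis as its only operational criterion. The second is "neonatal death within the first 24 h of life". A literature reference is attached to the definition.

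Under Interventions, the package covers "neonatal resuscitation (using upright bag-masks® [34], NeoBeat® newborn heart rate meters and NeoNatalie live training manikins". The Abstract (Methods) says that the heart rate monitors "will be introduced in the hospitals to identify fetal distress during labor and to improve neonatal resuscitation", so newborn heart rate measurement arrives as part of the package. A secondary outcome looks at the same kind of infant: "Proportion of non-breathing babies who receive a bag and mask ventilation within 1 min of birth".

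Under Data collection, "data on mortality and clinical events during intrapartum care will be collected from patient case notes and labor and delivery registers". Eligibility requires a fetal heart sound at admission, which says nothing about the infant's state at birth. No section adds absence of heartbeat or other signs of life to the stillbirth criterion, excludes infants being ventilated, or reclassifies an infant who later breathes or survives.

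**The concern.** Absence of breathing at a fixed time describes respiratory effort, not vital status. An infant can be apnoeic at 10 minutes, have a heartbeat, be ventilated and live. Under the stated criterion that infant enters the numerator of a mortality outcome.

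These infants are the ones on whom bag-mask ventilation, heart rate meters and resuscitation drills are meant to act. The number of infants in this state at 10 minutes, and how staff record them, could therefore differ between control and intervention periods. If the numbers are equal, the relative effect is diluted. If they differ, the estimated effect is biased.

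**Working it through.** **Step 1: which infants does the definition misclassify?** The table applies the written rule and a vital-status rule (not alive at 24 h) to the possible cases, all with fetal heart sound at admission.

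| Infant | Rule as written | Vital status at 24 h |
|---|---|---|
| No signs of life at birth, not revived | event | event |
| Heartbeat, not breathing at 10 min, dies at 5 h | event (meets both components) | event |
| Heartbeat, not breathing at 10 min, alive at 24 h | **event** | **not an event** |
| Breathing at 10 min, dies within 24 h | event | event |
| Breathing at 10 min, alive at 24 h | not an event | not an event |

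Only the third row differs. In the second row the infant is an event under both rules; only the component to which it is assigned is uncertain.

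**Step 2: baseline.** The plan gives no figure for the third row, so there is no stated number to reproduce. For scale, the printed Table 1 rates are weighted by births:

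(5464×13.7 + 14,300×34.9 + 11,006×11.0 + 8649×23.5 + 3112×14.7 + 3847×30.0 + 4132×36.5 + 6277×27.9) / 56,787 = 1,385,347 / 56,787 = 24.4 per 1000.

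The Abstract's 15% change is then 0.15 × 24.4 = 3.66 per 1000, giving 20.74 per 1000 under intervention. (For Seti Zonal Hospital the two component rates sum to 31.9, while the printed total is 27.9. Using 31.9 adds 6277×4.0 = 25,108 to the numerator and gives 24.8 per 1000. The results below then change by at most about 0.1 percentage point.)

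**Step 3: effect on the observed reduction.** Let m_C and m_I be the surviving infants per 1000 counted as deaths in control and intervention periods. Both are assumed values.

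Observed reduction = 1 − (20.74 + m_I) / (24.40 + m_C)

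| m_C | m_I | Calculation | Observed reduction |
|---|---|---|---|
| 0 | 0 | 1 − 20.74/24.40 | 15.0% |
| 1 | 1 | 1 − 21.74/25.40 | 14.4% |
| 5 | 5 | 1 − 25.74/29.40 | 12.4% |
| 1 | 2 | 1 − 22.74/25.40 | 10.5% |
| 2 | 1 | 1 − 21.74/26.40 | 17.7% |

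**Step 4: sample size in the equal case.** A plain comparison of two proportions (one-sided 5%, 90% power, before design effect and loss) needs 28,211 per group at 24.4 per 1000 with a 15% reduction. With 1 per 1000 misclassified in both periods it needs 29,431, a ratio of 1.04. This shows scale only; it does not reproduce the plan's McNemar-based figure.

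**The case against.** The strongest reply is that the parenthesis qualifies the word stillbirth within an outcome named mortality. Data come from case notes and registers, where a surviving infant would not normally be entered as a stillbirth, and no section describes recoding from a 10-minute breathing field. The cited reference, which is not shown, may carry a fuller definition. The article also does not say whether breathing means spontaneous breathing.

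This limits what can be said about conduct: a reader might infer that survivors will in fact be recorded as deaths, and the documents do not show that. It does not repair the wording. The article states one criterion, and that criterion can be met by a living child. If abstractors use something else, the written definition is not the one applied.

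Three further inferences are tempting and not supported:

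- **That the bias runs against an effective package.** More infants might be under ventilation at 10 minutes in intervention periods, but better resuscitation could also leave fewer infants not breathing by then. The direction is open.
- **That a large share of the target effect is lost.** A difference between periods of 0.5 to 2 per 1000 would be 14% to 55% of 3.66 per 1000, but nothing in the documents supports a difference of that size. Weighted in the same way, the Table 1 intrapartum stillbirth rate is 468/56,787 = 8.2 per 1000. A difference of 2 per 1000 would be about a quarter of it (2/8.2 = 24%) and would exceed the whole rate of 1.2 at Bheri Zonal Hospital.
- **That infants meeting both components are counted twice.** Sample size treats the outcome as binary, so such an infant is one event.

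**Conclusion.** The point stands as a defect in a stated definition. The stillbirth component is tied to breathing at 10 minutes with no sign-of-life criterion, so an infant alive after 24 h can be a primary-outcome event, within the group the package targets.

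The size is unknown. Under the assumed rates, equal misclassification of 1 per 1000 costs little (15% becomes 14.4%). A difference of 1 per 1000 between periods moves the observed reduction to 10.5% or 17.7%, depending on which period has more. These figures rest on the printed Table 1 rates, a true 15% reduction and assumed counts of misclassified survivors. They show sensitivity and do not estimate bias. The definition is worth correcting because the correction costs very little, not because a large distortion has been shown.

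**What to change.** Define the primary event by vital status: not alive at 24 h after birth, among births with fetal heart sound at admission, counted once per infant. No survivor can then be an event, and the total no longer depends on where the line between stillbirth and early neonatal death is drawn.

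Report the two components descriptively, with the same recorded sign-of-life criteria in control and intervention periods. State alongside them that newborn heart rate meters are introduced with the package: a heartbeat may be detected more often in intervention periods, so the split may be ascertained differently even under identical written criteria. Breathing status at 10 minutes can be kept as a descriptive item.

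The cost is a change of wording and confirmation that 24 h vital status is abstracted for every birth, which the second component already requires. Applying sign-of-life criteria to the split also depends on what control-period case notes record, which is a further reason to keep the split descriptive. No extra participants or procedures are needed.

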### Sample size

The intervention will be employed in the same hospital. Therefore, every hospital will be included in control as well as intervention groups. This fact will produce the correlated data between the arms. For binary correlated data, we have considered the one-sided McNemar’s test for sample size calculation. Considering the statistical power of 90%, level of significance at 5% and the average cluster size of 4800 deliveries we have calculated the sample size. For adjusting the cluster effect, the sample size is adjusted by the design effect. The design effect is chosen as a proxy of 1.71 based on Nepal’s Demographic Health Survey 2016 [37]. This design effect is updated based on our average cluster size. The design effect for NMR in NDHS 2016 is reported as 1.12 for urban sample with an average cluster size of 799. Based on the information, we have calculated the intra-cluster correlation coefficient (ICC) of 0.00015 which gives the design effect 1.71 for average cluster size 4800 [38]. We have also considered the 7% loss to follow up to reach the final sample size of 31,259 deliveries in each group. This number will be proportionally allocated among the hospitals. The STATA command “power” is used for necessary calculation.

Purposive sampling will be used in the qualitative components of the study. Maximum variation sampling will guide the selection of participants to in-depth interviews with health workers and focus group discussions with the hospital management team. This approach secures a wide variety of people of interest and consequently a broad range of perspectives to better understand contextual factors influencing on implementation. A convenient sample of pregnant women will be interviewed about their experiences of intrapartum care. Sample sizes will be based on data saturation (Table 2).

**Table 2 Tab2:** Number of health workers in the study hospitals (2017)

	Nurses	Doctors	Other health workers	Total health workers
Koshi Zonal Hospital	25	8	45	78
Janakpur Regional Hospital	60	22	0	82
Bharatpur Hospital	86	20	17	123
Lumbini Zonal Hospital	81	7	36	124
Dadeldhura Sub-Regional Hospital	42	2	13	57
Mid-Western Regional Hospital	20	3	22	45
Bheri Zonal Hospital	33	4	26	63
Seti Zonal Hospital	32	6	56	94

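### The stated 90% power holds only for an unexplained one-sided 5% test; if that 90% is right, a two-sided 5% test has about 83%, and the abstract mentions neither sidedness nor direction

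*Protocol article*

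**What the plan says.** The Sample size section of the protocol article names the test behind the calculation: the authors "considered the one-sided McNemar’s test for sample size calculation". It then gives the operating values: "Considering the statistical power of 90%, level of significance at 5% and the average cluster size of 4800 deliveries". A design effect of 1.71 and 7% loss to follow-up lead to 31,259 deliveries in each group. The section gives no reason for one-sidedness and does not name the direction of the single tail. It also omits the baseline death rate and the discordant proportions that a McNemar calculation needs.

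The Methods part of the abstract summarises the same calculation as "With a level of significance of 95%, the statistical power of 90% and an intra-cluster correlation of 0.00015" and concludes that "a study period of 19 months should detect at least a 15% change in intrapartum-related mortality". It mentions neither sidedness nor direction, and the 95% can only be a confidence level put in place of the significance level.

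The objectives, at the end of the Background, speak neutrally of the impact of the package on intrapartum-related mortality. The Data analysis section names no test for the primary outcome and leaves the analysis strategy until the data have been collected.

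**The concern.** A reader of the abstract would take 90% power for a change in mortality at 5% to mean the conventional two-sided test, matching a 95% confidence interval. The calculation underneath puts the whole 5% in one tail, which is an easier target. The abstract and the Sample size section therefore describe different standards of evidence for the same number of deliveries.

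The primary outcome is death, and the article intends the results to guide policy and scale-up. Nothing in it argues that an increase in deaths is impossible or of no interest. What is at stake is whether the advertised power is the power of the analysis that will be reported, and whether that analysis can point either way.

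**Working it through.** **Inputs from the article.** One-sided test, 5% significance, 90% power, design effect 1.71, 7% loss, 31,259 deliveries per group (Sample size); 15% change (abstract). The 15% is read here as a relative reduction, which is an assumption.

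**Step 1: can 31,259 be reproduced?**
- The quoted ICC gives a design effect of 1 + 4,799 × 0.00015 = 1.72, in line with the stated 1.71.
- Removing the plan's adjustments leaves 31,259 × 0.93 / 1.71 ≈ 17,000 deliveries per group. This figure is back-calculated and does not appear in the article.
- The McNemar formula is n = [z_α √s + z_β √(s − d²)]² / d², where s is the sum of the two discordant proportions and d their difference.
- The baseline rate has to be assumed. The birth-weighted mean of Table 1 is 24.4 per 1000 (hospital range 11 to 36.5). A 15% relative reduction gives 20.7 per 1000 and d = 0.00366. With no pair correlation, s = 0.0441.
- Then n ≈ 28,213, and 28,213 × 1.71 / 0.93 ≈ 51,900 per group, not 31,259.
- Reaching 31,259 one-sided takes a pair correlation of about 0.40 at that rate, or a baseline of about 40 per 1000 with no correlation. The article states neither.

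So the stated sample size cannot be confirmed, and the next step takes the stated 90% as given.

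**Step 2: convert one-sided to two-sided at the same sample size.**
- The standardised effect implied by 90% power at one-sided 5% is 1.6449 + 1.2816 = 2.9264.
- The two-sided 5% critical value is 1.9600.
- Power is Φ(2.9264 − 1.9600) = Φ(0.9664) = 0.833.

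This needs no baseline rate or pair correlation, because it depends only on the significance level and the stated power. As a check, every combination of rate and correlation solved to give 31,259 at one-sided 5% and 90% also gave 83.3% two-sided.

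**Step 3: the same gap in other units.**
- Type II error rises from 10% to about 17%.
- At two-sided 5% and 90% power, the detectable effect grows by a factor of (1.9600 + 1.2816) / 2.9264 = 1.108. A 15% reduction becomes roughly 15% × 1.108 = 16.6%, or about 16.5% once the smaller variance at the lower rate is allowed for.
- Holding both 15% and 90% would need 1.108² = 1.227 times the deliveries, about 38,350 per group.

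**Step 4: sensitivity if the 90% is not taken at face value.** Assume a 15% relative reduction, no pair correlation and 17,000 deliveries per group after adjustments. Power is then Φ[(d√n − z_α √s) / √(s − d²)].

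| Assumed baseline per 1000 | One-sided 5% | Two-sided 5% |
|---|---|---|
| 11 (lowest hospital) | 45% | 33% |
| 24.4 (weighted mean) | 73% | 62% |
| 36.5 (highest hospital) | 87% | 80% |

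These values depend on the assumed rate and correlation. They show that sidedness costs power whatever the truth about the 90%.

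**The case against.** The strongest reply is that the one-sided basis is openly disclosed and applies to the sample size only. No section fixes a one-sided primary test. A reader might infer that the trial as planned cannot report harm, but the article does not support that: it would follow only if the final test copied the sample-size basis. This part of the objection stands.

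It follows that the possible consequences are alternatives. A doubled false-positive rate for benefit and an inability to declare harm both require a one-sided final test, in which case sidedness takes nothing from the 90%. The 83% requires a two-sided final test, in which case false positives are not doubled and harm can be declared. They should not be charged together.

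The 83% also accepts a 90% that could not be reproduced, so it is not an estimate of the trial's true power. That limit stands too.

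A further temptation is to read the secondary outcome "Proportion of deliveries resulting in emergency cesarean sections and instrumental deliveries due to fetal distress" as an admission that the package alters operative delivery and might raise deaths. The article only lists it as something to measure. It is also fair to say that a reduction is a change, so the abstract's wording is incomplete and does not flatly contradict the Sample size section.

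Finally, more births may accrue than the target. Table 1 sums to 56,787 births a year. Over 19 months less a 2-month transition, that is 56,787 × 17 / 12 ≈ 80,400, or about 40,200 per condition if split evenly. Consent, eligibility and an uneven split would lower this, and the article's power statement rests on 31,259.

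None of this removes the core point: the advertised 90% does not hold for a two-sided 5% test at the stated sample size, and no reason is given for the one-sided basis.

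**Conclusion.** The point holds in a limited form. The Sample size section supports 90% power only for a one-sided 5% McNemar test, without justification. The abstract offers the same 90% for an undirected change and misstates the significance level.

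If the stated 90% is right, two-sided 5% power at 31,259 per group is about 83%. Which consequence follows depends on a final test that the article leaves open:

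- **Two-sided:** the 90% is overstated by about 7 percentage points.
- **One-sided for a reduction:** the false-positive rate for benefit is 5% rather than 2.5%, and an increase in deaths could not be declared.

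Two stronger conclusions are not supported. The article does not plan a test that is blind to harm, and the conversion does not show that more women must be enrolled. The missing baseline rate and discordant proportions behind 31,259 are a separate and larger problem, which the conversion neither solves nor depends on.

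**What to change.** - Specify the primary test as two-sided at 5%, reported with a 95% confidence interval.
- In both the abstract and the Sample size section, restate the power (about 83% on the plan's own basis) or the reduction detectable with 90% power (about 16.5%, reading the 15% as relative).
- In the abstract, change the significance level from 95% to 5% two-sided and state the direction of the effect used for planning.
- If the one-sided test is kept instead, justify it, name its direction, and still report a two-sided 95% interval.

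The cost is wording and a less favourable stated power. Enrolment does not need to change.
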